### Adverse Events

From the signing of informed consent to the end of the study, all adverse events that the investigator considers related to the study procedures will be recorded.

As part of the medical history, health problems (including clinically significant vital analytical values or constants located outside the reference range) that were diagnosed or known before the signing of informed consent will be recorded.

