### Sample Size

In total, the inclusion of 12 lung transplant recipients is planned. Currently, there are no data in the scientific literature about the pulmonary disposition of ISA. The number of subjects has been estimated based on the objective and characteristics of the study and the drug under study. Given the descriptive nature of the study and previous similar studies [9,10], it has been considered that with the exposure of 12 subjects, the precision of the estimates will be sufficient to determine the pharmacokinetic profile of oral ISA at the bronchopulmonary level.

Patients eligible for inclusion in this study must meet all the inclusion criteria and should not meet any of the exclusion criteria (Textbox 1).

Inclusion and exclusion criteria.

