### Intervention

The trial has been approved as a “low interventional clinical trial” according to the definition in the European Clinical Trials Regulation (536/2014), because the investigational medicinal product is used in accordance with the terms of the marketing authorization, and the additional diagnostic or monitoring procedures do not pose more than minimal additional risk or burden to the safety of the subjects compared to normal clinical practice.

All participants included will receive the product under investigation—oral ISA—at the doses and dosage regimen stated in the Summary of Product Characteristics: loading dose of 200 mg/8 h for the first 48 hours and maintenance dose from day 3 at 200 mg/24 h.

After 5 days of treatment with ISA and before the treatment is discontinued, patients will be randomized to perform the scheduled bronchoscopy at different times from the administration of ISA with the following distribution:

Group 1 (n=3): 2 hours from the administration of ISAGroup 2 (n=3): 4 hours from the administration of ISAGroup 3 (n=3): 8 hours from the administration of ISAGroup 4 (n=3): 12 hours from the administration of ISA

Furthermore, 4 blood samples will be obtained per patient: at 72 hours after treatment initiation, on the day of the bronchoscopy, at the time of the BAL (simultaneously), and at 7 days after treatment initiation, to analyze tacrolimus and ISA plasma levels.

There is no restriction regarding the use of medications and concomitant therapies. All medications (except study medication) and nondrug therapies administered during the study should be listed in the corresponding section of the concomitant medication case report form (CRF). The use of any concomitant treatment will be carried out according to the authorized conditions of use or, failing that, according to the usual clinical practice.

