#### Secondary End Points

For interaction evaluation, tacrolimus and mycophenolate concentrations will be determined before treatment and at 72 hours, 96 hours, and 7 days from the initiation of ISA treatment. The percentage of patients who required dose adjustment of the immunosuppressive drug after the start of treatment with ISA and the magnitude of the adjustment will be determined.

Safety will be assessed by recording adverse effects, the physical examination of patients, and analytical results.

A systematic description of all adverse events recorded during the follow-up will be performed. Listings of adverse events, previously coded by the Medical Dictionary for Regulatory Activities and grouped by organ or systems according to severity, intensity, and causal relationship with the study medicinal products, will be included.

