### Statistical Analysis

The statistical analysis will be carried out following the principles specified in the International Conference on Harmonization Topic E9 (CPMP/ICH/363/96). The data will be analyzed using the SPSS statistical software (version 22.0; IBM Corp).

Given the characteristics of the study—a descriptive study—only 2 analysis groups are planned: (1) the safety and tolerability analysis group, which will include all patients who have received at least 1 dose of ISA; and (2) the pharmacokinetic analysis group, which will include all patients with BAL samples from bronchoscopy.

Demographic data and other data related to patient selection will be descriptively summarized for the pharmacokinetic analysis group and the safety and tolerability group. Categorical data will be presented in the form of frequencies and percentages. For continuous data, descriptive statistics such as mean, median, and SD or median, IQR, minimum, and maximum will be presented.

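### Adverse events are recorded only if judged related to study procedures, but the safety end point classifies them by relationship to the drug, so the safety listing is selected at source

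*Protocol article*

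**What the plan says.** The Adverse Events section of the protocol article gives the only rule on which events are captured. It runs from signature of consent to the end of the study, and under it "all adverse events that the investigator considers related to the study procedures will be recorded". The rest of that section deals with conditions known before consent, which go into the medical history.

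The Secondary End Points section treats safety as an end point: "Safety will be assessed by recording adverse effects, the physical examination of patients, and analytical results". It continues: "A systematic description of all adverse events recorded during the follow-up will be performed". The listings are to be coded with MedDRA and "grouped by organ or systems according to severity, intensity, and causal relationship with the study medicinal products".

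The Statistical Analysis section plans two analysis groups. One is "the safety and tolerability analysis group, which will include all patients who have received at least 1 dose of ISA".

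*Study procedures* is not defined. Two other places bear on its meaning:
- The Intervention section, in justifying low-interventional status, deals first with the product and its marketing authorisation. It then says separately that "the additional diagnostic or monitoring procedures do not pose more than minimal additional risk or burden".
- The inclusion criteria ask for willingness and ability to keep to visits, the treatment plan and laboratory tests, followed by *other* study procedures.

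**The concern.** An adverse event listing supports a statement about a drug only if events enter it independently of the judgement that the listing is meant to report. Here an event must pass two conditions first: the investigator must judge it related, and related to study procedures. The listing is then to be classified by relationship to isavuconazole. Nothing in the article says that drug-related or unrelated events are also entered.

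At stake is the safety end point and the main content of one of the two analysis groups. The trial is open-label with a single arm, so no comparator would reveal or offset the loss. A causality grade given after full capture can be reviewed later. An event that was never entered cannot, unless it is documented elsewhere.

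**Working it through.** The plan states no figure to reproduce, and no sample size, power or event rate enters the point. The check is to set the capture rule beside the reporting rule.

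**Step 1. The two rules.** Capture (Adverse Events) asks whether the event is related to study procedures. Reporting (Secondary End Points) asks how the event is related to the study medicinal products.

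**Step 2. All possible events.** Cross relationship to isavuconazole with relationship to the other procedures (bronchoscopy, lavage, sampling), and ask which events are entered under each reading of *study procedures*.

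| Related to isavuconazole | Related to another procedure | Narrow reading: drug is not a procedure | Broad reading: treatment plan is a procedure |
|---|---|---|---|
| yes | yes | recorded | recorded |
| yes | no | **not recorded** | recorded |
| no | yes | recorded | recorded |
| no | no | **not recorded** | **not recorded** |

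**Step 3. Narrow reading.** The Intervention section supports it by keeping the product apart from the additional procedures. The second row, reactions attributed to the drug alone, is lost. Bronchoscopy comes only after 5 days of treatment. A patient who reacts to the drug before then has received at least 1 dose and so belongs to the safety group, but the reaction is not entered unless it is attributed to some procedure.

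**Step 4. Broad reading.** The inclusion criteria leave room for it. Drug reactions are now entered, but the fourth row is still lost. The *not related to isavuconazole* category can hold only events attributed to another study procedure. An event that the investigator attributes to nothing in the study is absent, so total incidence is understated and the drug-causality grading is partly settled at entry.

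**Step 5. Common result.** The fourth row is missing under both readings and the second under one of them. Under neither does the listing hold all adverse events in treated patients.

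**Step 6. Size.** The proportion lost is 1 minus the proportion of events that pass the filter. The article gives no event counts and no share of events related to procedures, so no value follows.

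**The case against.** The strongest defence has five parts.

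1. *The wording may be condensed.* The article summarises a full approved protocol that is not shown. This cannot be checked. The article does not leave the rule unstated, however: it states one, and that rule conflicts with the end point it also states.
2. *Study procedures may include treatment.* This is a fair reading. A reader might infer that the count of drug-only reactions is zero by construction, but that holds on the narrow reading only. The defence does not restore events judged unrelated.
3. *The end point covers events recorded.* A reader might infer that the safety end point cannot be produced at all. The text does not support that: "A systematic description of all adverse events recorded during the follow-up will be performed". A listing can be printed, but it would be a selected one.
4. *Other safety data are not filtered.* Physical examination and analytical results are collected independently of the rule, and signs of toxicity may appear there. This limits the harm but does not supply the causality-classified event listing.
5. *The stakes are modest.* Safety is a descriptive secondary end point, "In total, the inclusion of 12 lung transplant recipients is planned", and the product is used within its authorisation. All of this stands and bears on priority. Low-interventional status might be offered as a reason for lighter recording, but the article does not argue this, and it would not make the two sections agree.

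Three further inferences should be avoided.
- A percentage loss: assuming that 50% to 10% of events relate to procedures gives 100 − 50 = 50% to 100 − 10 = 90% lost, which only restates the assumption.
- A causality column with no contrast: on the narrow reading a procedure-related event can still be graded related or unrelated to the drug. On the broad reading the unrelated category is depleted but not necessarily empty.
- A conflict with the safety group definition as such: it says which patients are analysed, not which events are captured.

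**Conclusion.** The recording rule is wrong as written. Under either reading of *study procedures*, investigator judgement selects the adverse event listing before entry, and the listing cannot describe isavuconazole safety as the Secondary End Points section intends. On the narrow reading it omits drug reactions not attributed to a procedure as well as unrelated events. On the broad reading it omits unrelated events only. The direction is an undercount wherever such events occur; its size cannot be derived from the document.

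The conclusion assumes that sites follow the rule as printed and that no wider rule applies elsewhere. If fuller recording took place in practice, the Adverse Events section misdescribes it and still needs correction. The primary outcome, isavuconazole in epithelial lining fluid, is unaffected.

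**What to change.** Replace the recording sentence in the Adverse Events section with: *From informed consent to the end of the study, all adverse events are recorded regardless of causality. The investigator grades the relationship of each event separately to isavuconazole and to study procedures.* Separate grading also removes the need to settle whether treatment is a study procedure.

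The Results section reports enrolment complete with 13 patients, so new wording alone would change little in the data. For these patients, complete the adverse event entries from available source records. Do this before database lock, because the Data Management and Quality Control section does not allow changes afterwards. Mark retrospectively entered events as such, and report that events not documented in the source records cannot be recovered.

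The cost is a one-sentence amendment plus a record review for 13 patients. The article says that patients will be hospitalised, which helps, but it does not say that inpatient records reach to the end of the study, so recovery may be incomplete. If all events were in fact recorded, only the text needs correcting.

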### Data Management and Quality Control

All records will be collected in a CRF, which will be completed by a trained and qualified investigator. Once a CRF is completed, the original record will not be changed if any corrections are made. The completed CRF will be reviewed by the clinical monitor.

Data entry and management will be guided by medical statistics experts. After reviewing and confirming that the established database is correct, the data will be locked by the main researchers and statistical analysts. The locked data or files will not be changed thereafter and will be submitted for statistical analysis by the research group. The Clinical Trial Unit of Instituto de Investigación Sanitaria Puerta de Hierro-Segovia de Arana, which does not have any competing interests, will be responsible for monitoring the data.

The study will be safely conducted in accordance with the protocol and applicable regulatory requirements under Good Clinical Practice, and data collection will be properly executed.

### Statistical Analysis

The statistical analysis will be carried out following the principles specified in the International Conference on Harmonization Topic E9 (CPMP/ICH/363/96). The data will be analyzed using the SPSS statistical software (version 22.0; IBM Corp).

Given the characteristics of the study—a descriptive study—only 2 analysis groups are planned: (1) the safety and tolerability analysis group, which will include all patients who have received at least 1 dose of ISA; and (2) the pharmacokinetic analysis group, which will include all patients with BAL samples from bronchoscopy.

Demographic data and other data related to patient selection will be descriptively summarized for the pharmacokinetic analysis group and the safety and tolerability group. Categorical data will be presented in the form of frequencies and percentages. For continuous data, descriptive statistics such as mean, median, and SD or median, IQR, minimum, and maximum will be presented.

## Results

The enrollment for the PBISA01 trial began in October 2020 and was completed in October 2021. Thirteen patients have been enrolled in this clinical trial. No data regarding the pharmacokinetic profile of ISA has been analyzed yet. The results are expected to be published in October 2022.

## Discussion

### Expected Findings

There are no clinical studies that analyze the bronchopulmonary penetration of ISA. Our hypothesis is that the bronchopulmonary penetration of ISA in lung transplant recipients may be compromised as a result of poor vascularization and local inflammatory phenomena.

In this sense, the BAL performed routinely in the follow-up of lung transplant recipients constitutes an opportunity to analyze the bronchopulmonary penetration of ISA. The simultaneous determination of the levels of ISA in plasma and the ELF obtained through the BAL can be useful to determine its penetration at the bronchopulmonary level and correlate it with the response to treatment [13]. This aspect is especially relevant as the lung transplant recipients are a population that is especially susceptible to the development of IFD.

The use of BAL samples as surrogates of ELF and alveolar macrophages exposure of ISA requires the development of a sensitive method of analysis. The proposed chromatographic method includes one important advantage: the dual detection of UV and fluorescence. The fluorescence detection results in sensitivities between 1 and 3 orders of magnitude higher than absorption methods.

It is well-accepted that penetration into the site of infection to achieve microbe-eliminating concentrations is a key requirement for the efficacy of all antimicrobial agents [14]. The concentration of ISA within the lung ELF may provide a good estimate of drug exposure for the treatment of IFD [12]. However, the monitoring of ISA concentration in the ELF via bronchoscopy is not practical in the clinical setting, so the use of plasma ISA concentration as a surrogate for the ELF concentration is a good alternative.

The pharmacokinetics of ISA has been studied as an experimental treatment of invasive aspergillosis in neutropenic rats. In one study [15], the subjects treated with ISA had a lower residual fungal load after treatment, lower lung damage, greater survival, and lower levels of (1,3)-β-D-glucan, both in plasma and the BAL.

Other physiological factors such as the presence of inflammation and changes in vascularization substantially influence the exposure of drugs at the site of action. This aspect is especially relevant in the lung transplant recipient in which the absence of bronchial revascularization and local inflammatory phenomena secondary to ischemia and reperfusion can hinder the tissue penetration of drugs.

The design of the study includes the randomization of the patients to perform the scheduled bronchoscopy at different times after dose intake. This is a suitable design to collect ISA pulmonary concentration at different timepoints without interfering with the scheduled dosage and with no additional burden to the patient. The number of subjects has been estimated based on the objective and characteristics of the study and the drug under study. Given the descriptive nature of the study and previous similar studies [9-11], it has been considered that with an exposure of 12 subjects, the precision of the estimates will be sufficient to determine the pharmacokinetic profile of oral ISA at the bronchopulmonary level.

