### Outcome Measures

#### Primary End Point

The primary outcome is the measurement of ISA in the ELF. ISA concentrations will be measured in plasma ELF and alveolar macrophages by a high-performance liquid chromatography/UV coupled to fluorescence method. ISA levels in the ELF and alveolar macrophages will be obtained from the BAL. The proposed chromatographic method will allow the quantification of ISA in the clinical samples after a first step of protein precipitation and the direct injection (plasma) of resulting supernatant. For BAL samples, a previous step of sample concentration will be required to increase the sensitivity of the method. The analytical run will result in the specific characterization and robust quantification of this triazole by its UV and fluorescent profile.

Data from the cell count, percentage of alveolar cells, and volume of cell-lining fluid will be presented for the different times when bronchoscopy is performed. The volume of cell-lining fluid will be estimated using the concentration of urea in plasma and BAL from the following formula [13]: *estimated ELF volume = amount of total urea in BAL (mg) / plasma urea concentration (mg/mL)*. The area under the curve of ISA will be estimated at the ELF level. The concentration, time-dependent curves in the ELF will be calculated using noncompartmental analyses. The ratio between the ELF and plasma will be estimated from the average values of the patients included in each group.

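### Plasma is called a good stand-in for ELF before any data, and the one stated ELF-plasma comparison, a ratio of group averages, cannot show whether a patient's plasma level predicts that patient's ELF level

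*Protocol article*

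**What the plan says.** The surrogacy statement is in the Discussion of the protocol article, under Expected Findings. Its only premise is that "the monitoring of ISA concentration in the ELF via bronchoscopy is not practical in the clinical setting", and from this it concludes: "so the use of plasma ISA concentration as a surrogate for the ELF concentration is a good alternative". The sentence carries no citation and no hedge.

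The same section says "There are no clinical studies that analyze the bronchopulmonary penetration of ISA". It gives as the trial's hypothesis that "the bronchopulmonary penetration of ISA in lung transplant recipients may be compromised as a result of poor vascularization and local inflammatory phenomena", and adds: "Other physiological factors such as the presence of inflammation and changes in vascularization substantially influence the exposure of drugs at the site of action". The Results section says: "No data regarding the pharmacokinetic profile of ISA has been analyzed yet".

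On analysis, the Primary End Point section states one ELF-plasma comparison: "The ratio between the ELF and plasma will be estimated from the average values of the patients included in each group". The Intervention section sets four groups of three patients, at 2, 4, 8 and 12 hours after dosing. One of the four blood samples per patient coincides with the lavage, so every patient with a usable lavage has a simultaneous plasma-ELF pair.

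**The concern.** Using plasma in place of ELF is a claim about individuals: a patient's plasma level must predict that patient's ELF level well enough to be useful. The article asserts this on grounds of convenience. If local inflammation and vascularization shape exposure in the graft, whether the ELF/plasma ratio is similar from patient to patient is an open question.

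The stated comparison averages ELF and plasma separately within each group before dividing, so it never uses the link between a patient's two values. A reader could take reassuring group ratios as support for a sentence already in print, and plasma monitoring in place of ELF is a conclusion that clinicians might act on.

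**Working it through.** **Inputs from the article.** Planned N = 4 groups × 3 = 12, which agrees with the Sample Size section; 13 patients were enrolled (Results). The article gives no SD, correlation, precision target or surrogacy criterion, so there is no figure of its own on this point to reproduce. All CVs below are assumptions.

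**1. The ratio of averages is blind to pairing (no distributional assumption).** Take one group with plasma 2, 3, 4 and ELF 1, 1.5, 2 in any units. The ratio of averages is (4.5/3)/(9/3) = 1.5/3 = 0.50. Reassigning the ELF values among the three patients changes neither average:

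| ELF for plasma 2, 3, 4 | Ratio of averages | Within-group r | Individual ratios |
|---|---|---|---|
| 1, 1.5, 2 | 0.50 | +1.0 | 0.50, 0.50, 0.50 |
| 1, 2, 1.5 | 0.50 | +0.5 | 0.50, 0.67, 0.38 |
| 1.5, 1, 2 | 0.50 | +0.5 | 0.75, 0.33, 0.50 |
| 1.5, 2, 1 | 0.50 | -0.5 | 0.75, 0.67, 0.25 |
| 2, 1, 1.5 | 0.50 | -0.5 | 1.00, 0.33, 0.38 |
| 2, 1.5, 1 | 0.50 | -1.0 | 1.00, 0.50, 0.25 |

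The planned figure is the same whether plasma predicts ELF perfectly or runs opposite to it.

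**2. What the spread of the four ratios can show.** Simulation of four groups of three, with log-normal plasma and ELF, assumed CV 50% each, and the same true median ratio at every time. The quantity is the largest divided by the smallest of the four group ratios:

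- log-scale correlation 0: median 2.2 (5th-95th percentiles about 1.4 to 4.2);
- log-scale correlation 0.9: median 1.3 (1.1 to 1.6).

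Wide spread therefore counts somewhat against a constant ratio. The two ranges overlap, however, and in real data a true change of ratio with time after dosing would also produce spread.

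**3. What the simultaneous pairs could show.** Fisher-z 95% interval: tanh(atanh(r) ± 1.96/√(n - 3)). For r = 0.7 and n = 12: atanh(0.7) = 0.867 and 1.96/√9 = 0.653, so the limits are tanh(0.214) = 0.21 and tanh(1.521) = 0.91.

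| Observed r | 95% CI, n = 12 | 95% CI, n = 13 |
|---|---|---|
| 0.5 | -0.10 to 0.83 | -0.07 to 0.82 |
| 0.7 | 0.21 to 0.91 | 0.24 to 0.90 |
| 0.9 | 0.67 to 0.97 | 0.69 to 0.97 |

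Adjusted for the four time groups (three further parameters, n = 12), r = 0.7 gives 0.07 to 0.93.

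**4. Uncertainty for one new patient's ratio.** Fold either way = exp(t × s × √(1 + 1/12)), with s = √ln(1 + CV²) and t(0.975, 11 df) = 2.201:

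- CV 30%: s = 0.294, about 2.0-fold;
- CV 50%: s = 0.472, about 3.0-fold;
- CV 80%: s = 0.703, about 5.0-fold.

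These pool all 12 patients around one common ratio.

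**The case against.** The strongest reply is that surrogacy is not an objective, endpoint or hypothesis of this trial. The aim is to describe penetration, the primary outcome is the drug measured in ELF, and a ratio of group averages is a legitimate summary of average penetration. The sentence is a Discussion remark about monitoring in practice. This stands: the point is not a flaw in the primary analysis. But the remark is still made without evidence, and the stated method discards information already being collected.

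A reader might infer that the surrogacy sentence contradicts the trial's hypothesis. The article does not support that. The hypothesis is hedged and concerns the level of penetration, and a low but consistent ratio would still let plasma serve as a proxy.

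A reader might also infer that the claim would survive whatever the data show, or that group ratios would look stable with no plasma-ELF association. That is too strong. Under the step 2 assumptions with zero correlation, averaging the four ratios does give a steady-looking result (median 1.06, 5th-95th percentiles 0.76 to 1.48), but the article does not plan that average. The four separate ratios would typically differ about 2.2-fold, and by more than 1.5-fold in 89% of simulated trials. The article states no way to read that spread.

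Finally, the article is condensed, and the full protocol or SAP may contain a paired analysis. If so, only the wording of the article needs attention. The mere absence of a regression from the article is not the complaint.

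**Conclusion.** The point holds as a minor one about a stated method and one sentence. Surrogacy is inferred from impracticality alone, before any data, and the article's single stated ELF-plasma comparison cannot show whether plasma predicts ELF within a patient. The pairing result is exact and rests on no assumption. Spread across the four ratios is only a weak signal against a constant ratio.

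A patient-level analysis would address the right question but would not settle it: with 12 or 13 pairs even a correlation of 0.7 leaves a wide interval. The 2- to 5-fold prediction range depends on assumed CVs of 30% to 80%, for which the article gives no figures. The primary endpoint and the descriptive aim are unaffected.

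**What to change.** In the Primary End Point section, alongside or in place of the ratio of averages, compute each patient's ELF/plasma ratio from the simultaneous samples. Summarise these on the log scale: geometric mean with 95% CI, between-patient CV and range. Plot log ELF against log plasma with points marked by time group, and give the residual SD and the 95% prediction interval for an individual's ELF given plasma. Label this exploratory.

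Under Expected Findings, reword the sentence to say that whether plasma can stand in for ELF will be explored descriptively, and that no surrogacy claim will rest on group-average ratios.

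The cost is one analysis paragraph and one sentence, with no extra sampling. The downside is imprecision, which the intervals will make visible.
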